**Figure 1 figure1:**

Participant flow for the Survivorship App for Ethnically Diverse Black Prostate Cancer Survivors stratified randomized clinical trial.

### Study Randomization

This study will use a 1:1 stratified randomized controlled trial design and will enroll 248 participants who will be randomly assigned to either the SAFE-CaPS intervention group (n=124) or the control group (n=124) using REDCap’s stratified randomization module. Stratification will be based on ethnic background to ensure a balanced representation across study arms: native-born Black men (n=100), African-born Black men (n=74), and Caribbean-born Black men (n=74). Within each subgroup, participants will be randomized in equal numbers to the intervention and control arms (native-born Black men: 50/50; African-born Black men: 37/37; Caribbean-born Black men: 37/37). This stratified approach ensures balanced subgroup representation and supports exploratory analyses assessing potential differences in survivorship experiences and intervention response across ethnic backgrounds.

Due to the nature of the intervention, blinding of participants, care providers, and recruitment staff is not feasible. However, the data analyst will be blinded to group allocation to reduce analysis bias.

### Mobile Health Platform

The Insight mHealth Platform [58], developed by the SCC mHealth Technology Shared Resource [60], serves as the foundation for the SAFE-CaPS intervention. This state-of-the-art platform supports the rapid design, testing, and implementation of digital health studies, including secure EMAs, adaptive learning modules, automated symptom alerts, and provider notification tools, all within a HIPAA (Health Insurance Portability and Accountability Act)-compliant, encrypted infrastructure. EMA data are stored locally on study smartphones in a sandboxed, encrypted database and securely transmitted via encrypted channels to enterprise-grade Microsoft Azure servers, ensuring data confidentiality, integrity, and protection against unauthorized access. The platform has supported a broad portfolio of National Institutes of Health–funded clinical trials across cancer care, tobacco cessation, HIV prevention, chronic pain, and behavioral health [61-65], including studies specifically tailored for racial and ethnically diverse adults [61,66,67]. This evidence base demonstrates the platform’s scalability, cultural adaptability, and suitability for populations experiencing health inequities. Insight was selected for SAFE-CaPS because it provides oncology-specific safety features (eg, distress monitoring and nurse alerts), literacy-appropriate content options, and flexible cultural adaptation capabilities. The research team has collaborated closely with the mHealth Technology Shared Resource to develop and refine the SAFE-CaPS content and usability (Figure 2), ensuring alignment with study goals and adherence to clinical and ethical standards.

**Figure 2 figure2:**
[figure not shown]
Home page of the Survivorship App for Ethnically Diverse Black Prostate Cancer Survivors (SAFE-CaPS) app.

### Conceptual Frameworks

The SAFE-CaPS study is guided by an adaptation of the Revised WCM of QoL [47,48], which was informed by findings from our extensive integrative review [8] and prior qualitative studies [9,29,68]. The Revised WCM model provides a structured approach for understanding the impact of biological function, symptom experience, functional status, and general health perceptions on QoL among Black men with CaP [48]. The model posits that biological function (eg, CaP-related pathophysiology) influences symptom status (eg, urinary dysfunction, fatigue, and depression), which in turn affects functional status (eg, ability to perform daily activities) [48,69]. These factors shape an individual’s general health perception, ultimately determining their overall QoL, as measured by the Functional Assessment of Cancer Therapy-Prostate (FACT-P) questionnaire. The SAFE-CaPS intervention leverages this framework to enhance symptom monitoring, self-management, and early intervention to improve functional status and QoL outcomes.

Demographic factors (eg, age, education, ethnicity, income, marital status, and geographic residence) and clinical variables (eg, age at diagnosis, treatment type, disease stage, prostate-specific antigen level, family history, overall health perception, and comorbidities) may moderate the impact of the intervention on QoL. The integration of the WCM framework within the SAFE-CaPS intervention is designed to account for individual differences, ensuring a comprehensive, culturally tailored approach to improve QoL among Black survivors with CaP (Figure 3).

**Figure 3 figure3:**
[figure not shown]
Proposed model of treatment mechanism. PSA: prostate-specific antigen; QoL: quality of life; SAFE-CaPS: Survivorship App for Ethnically Diverse Black Prostate Cancer Survivors.

Additionally, the study incorporates the UTAUT framework to assess participant engagement and technology adoption [49]. The UTAUT model evaluates 4 key constructs that have been shown to influence behavioral intent and sustained app use (Figure 4) [49,70]. Performance expectancy refers to whether participants believe the intervention app will help them manage symptoms and improve their health behaviors. Effort expectancy captures perceptions of ease of use and overall accessibility. Social influence considers the extent to which health care providers, caregivers, and peers encourage engagement with the app. Facilitating conditions assess the availability of necessary resources and technical support to enable effective use of the intervention. Additionally, age serves as a moderating variable in the UTAUT model [49,70]. By integrating WCM for health outcomes and UTAUT for technology adoption, the study ensures a comprehensive evaluation of intervention effectiveness, allowing researchers to measure both clinical improvements in survivorship and behavioral factors affecting participant engagement. This dual-framework approach will inform future enhancements and scalability of the SAFE-CaPS intervention.

**Figure 4 figure4:**
[figure not shown]
Proposed Unified Theory of Acceptance and Use of Technology model.

### Intervention (SAFE-CaPS)

The SAFE-CaPS intervention is designed to provide real-time symptom monitoring and management of CaP-related symptoms while integrating culturally relevant content and psychosocial support. Acknowledging the importance of emotional well-being, the intervention includes resources for mental health support to improve coping with psychological challenges related to CaP survivorship.

The development of the SAFE-CaPS app was guided by a Community-Based Participatory Research approach, ensuring that the needs and lived experiences of Black men with CaP shaped its design and implementation [8,9,29,30]. The intervention is built upon findings from our prior work exploring QoL among ethnically diverse Black men with CaP [8,9,29]. This research identified key survivorship concerns, including symptom burden, psychosocial distress, and unmet informational needs, highlighting the necessity of a culturally responsive intervention. To increase relevance and usability, the app underwent iterative refinement in collaboration with a CAB composed of ethnically diverse Black men survivors with CaP [30]. Through focus groups, usability testing, and feedback from Black men experiencing CaP survivorship, the app was tailored to reflect their preferences, values, and health care experiences. Unique features include culturally relevant health education and an emphasis on peer support and interactions with trusted health care providers. Additionally, the intervention addresses historical health care mistrust by integrating educational modules that empower users to navigate the health care system and communicate effectively with providers.

A key feature of the SAFE-CaPS app is its incorporation of culturally tailored content, recognizing potential within-group differences among Black men from native-born, African-born, and Caribbean-born backgrounds. The intervention also acknowledges historical mistrust in health care and includes educational modules to enhance users' understanding of the health care system and encourage effective communication with providers. The intervention provides both dynamic and static resources, featuring content that adapts to user inputs and a comprehensive content library. The intervention also enables participants to log and share their symptoms with health care providers or designated proxies, supporting timely symptom reporting. Furthermore, the intervention uses behavioral engagement strategies, including push notifications and reminders, to encourage consistent participation. Using a longitudinal tracking approach, the SAFE-CaPS intervention captures detailed insights into the survivorship journey, including symptom burden, QoL, health behaviors (eg, physical activity, diet, and sleep), app usage patterns, and user-reported outcomes through weekly EMAs and quarterly follow-up surveys.

SAFE-CaPS includes daily assessments of key symptoms, including pain, sleep disturbances, fatigue, weight gain, urinary frequency and difficulty, bowel control issues, depression, anxiety, and worry. Participants also have the option to add additional comments in an open-text section to report any concerns or symptoms not captured in the standard items. Specific symptoms will trigger alerts based on frequency or distress levels, notifying both the study team and the designated health care providers selected by participants (Figure 5).

**Figure 5 figure5:**
[figure not shown]
Example ecological momentary assessment item from risk assessment (left) and adaptive educational material (right).

These alerts will prompt adaptive educational materials that provide self-management strategies until medical consultation is obtained (Figure 6). Specific alert triggers include urinary urgency, difficulty urinating, hematuria, constipation, blood in stool, pain, worry, or depression. Through these integrated components, SAFE-CaPS delivers a holistic and culturally responsive approach (developed with input from Black survivors with CaP and community advisors to ensure that language, imagery, and messaging reflect the lived experiences, preferences, and cultural values) to support Black men in navigating the complexities of CaP survivorship.

**Figure 6 figure6:**
[figure not shown]
Samples of educational content.

### Control Group (SC)

Participants in the control group will not have access to the SAFE-CaPS intervention content. Still, they will receive standard survivorship care, including routine medical follow-ups and referrals as needed through their health care providers.

### EMA

The SAFE-CaPS daily EMAs will include brief, real-time assessments of symptom status, functioning, and overall QoL. The goal is to minimize participant burden while capturing the essential data points necessary for the study’s analyses.

### Data Collection

Assessments will be conducted at baseline, post intervention, and interim time points at 3, 6, and 9 months. The assessment schedule is outlined in Table 1 (details of the assessment measures are provided in the Multimedia Appendix 3).

**Table 1 table1:** Overview of the questionnaire assessments.

EMA^a^ measures		Baseline (week 1)	Assessments (week 1-12)	Follow-up
**Weekly^b^ assessments (domains)**				
	Sociodemographic characteristics	✓		
	Clinical characteristics	✓		
	The positive and negative affect schedule	✓	✓	✓
**Daily assessments (domains)**				
	Pain level and impact	✓	✓	
	Sleep quality	✓	✓	
	Sexual functioning	✓	✓	
	Fatigue level	✓	✓	
	Weight gain	✓	✓	
	Urine frequency and difficulty	✓	✓	
	Bowel control	✓	✓	
	Physical activity frequency	✓	✓	
	Dietary records	✓	✓	
**Monthly^c^ assessments**				
	PHQ-4^d^	✓		✓
	FACT-P^e^	✓		✓

^a^EMA: ecological momentary assessment.

^b^For weekly assessments, the follow-up was done for months 6-12.

^c^For monthly assessments, the follow-up was done for months 3-12.

^d^PHQ-4: Patient Health Questionaire-4.

^e^FACT-P: Functional Assessment Cancer Therapy–Prostate.

### One-Time Assessments

At baseline, sociodemographic and clinical characteristics will be collected, including age, education level, ethnicity, marital status, geographic residence, and clinical history (eg, age at diagnosis, stage of cancer, treatment type, family history of CaP, treatment status, prostate-specific antigen level, and comorbidities).

#### Weekly EMAs

Mood will be assessed at baseline and weekly for the first 12 weeks and during the week following each QoL assessment at 3, 6, 9, and 12 months, totaling 15 weeks of evaluation. The Positive and Negative Affect Schedule will be used to measure affect, consisting of two 10-item scales assessing positive and negative mood [71]. Participants will rate the intensity of several dimensions of their affect on a 5-point scale (1=very slightly or not at all; 5=very much), with higher scores indicating greater positive or negative affect [71].

#### Daily EMAs

The SAFE-CaPS group will have access to the app-based intervention for 12 weeks. During this time, participants will complete daily assessments of various symptoms, including pain intensity and impact, sleep quality, fatigue levels, weight changes, urinary frequency and difficulty, body aches, bowel control, sexual function, and depression or anxiety. Additional measures will assess physical activity frequency, duration, and dietary intake (fruit and vegetable consumption). Participants will also complete daily EMAs for 1 week following their 6, 9, and 12-month QoL assessments. Each daily evaluation is expected to take approximately 5–10 minutes to complete.

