## Introduction

Prostate cancer (CaP) remains a leading cancer diagnosis among men in the United States, with 313,780 new cases and 35,770 deaths projected in 2025 [1]. Among racial groups, Black men have the highest incidence rates nationwide at 191.5 cases per 100,000 compared to 114.5 per 100,000 among white men, and a higher CaP mortality rate (37.2 vs 18.1 deaths per 100,000, respectively) [2]. Black men have a greater likelihood of more advanced or aggressive disease at diagnosis, and they are frequently diagnosed at later disease stages, which limits treatment options and contributes to higher morbidity and mortality rates [3,4].

Disparities in CaP survival among Black men are influenced by genetic susceptibility, limited access to health care, family history, socioeconomic factors, and delayed detection [5,6]. Despite these disparities, the overall 5-year survival rate for Black men with CaP is high at approximately 97% [2]. However, survival does not equate to optimal posttreatment outcomes, as many Black men experience a disproportionate burden of treatment-related complications, psychosocial distress, and lower quality of life (QoL) [4,7-9]. CaP survivorship presents unique and persistent challenges, particularly for Black men, who often face disproportionate burdens of physical, emotional, and social distress [5,10]. Long-term treatment-related side effects such as sexual dysfunction, bowel and urinary incontinence, and mobility impairments can significantly diminish QoL [11-14]. Additionally, concerns about cancer recurrence, medical mistrust, and limited access to survivorship resources create further barriers to effective coping and reintegration into daily life [15-17]. These issues are often intensified by stigma surrounding sexual dysfunction, cultural beliefs about masculinity, and discomfort discussing intimate symptoms, which can delay help-seeking among Black men [9]. Addressing these multifaceted survivorship needs requires culturally tailored interventions that improve symptom management and psychosocial support. While many survivors with CaP face physical and emotional challenges, Black men often experience lower levels of functioning in these areas compared to White men [18-20]. Studies report slower recovery rates, decreased satisfaction with recovery, and higher levels of regret following prostatectomy among Black men [3,21,22].

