Participants in the SAFE-CaPS intervention group who do not own a smartphone will be provided with an Android smartphone and basic cell phone service to ensure equitable access. Those who already own an Android or Apple smartphone will use their personal device. All participants randomized to the intervention will receive a unique, single-use code to download the Insight app developed by the SCC mHealth Technology Shared Resource [58]. Upon entering the code, they will complete the baseline assessment and have access to the app for a 12-month period. Participants will receive practical instructions on using the app from the research team and there will be an option for a video tutorial outlining the features, and a video tutorial outlining the app's features will be available during the initial visit. This tutorial video can be saved to the phone's home screen for future reference, if needed by the participants. Participants will also be instructed on how to exclude the Insight app from “Do Not Disturb” mode settings on Android and Apple devices to ensure that ecological momentary assessments (EMAs) are received and completed in a timely manner. This guidance aims to reduce missed notifications due to phone settings and enhance EMA completion rates. The Insight app will serve as the platform for assessment and intervention for study groups. During the baseline assessment, participants will receive instructions on app features and complete prompted EMAs. These instructions are also available on demand via the “App Instructions” button on the app's home screen. Participants will complete a weekly, app-prompted EMA throughout the study. The app will also prompt participants to complete follow-up surveys at months 3,6, 9, and 12. Additionally, a subset of participants in the intervention group (n=30) will be invited to schedule an exit qualitative interview with a research team member to gather feedback on their experiences using the app.

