### Study Compensation

Participants (N=248) will receive US $50 each for completing both the baseline and postintervention assessments, totaling US $100 per participant. In addition, all participants will receive US $25 for completing each interim survey at 3, 6, and 9 months (a total of US $75). Participants in the SAFE-CaPS arm who complete the semistructured exit interview (n=30) will receive an additional US $50 payment. To enhance EMA compliance, SAFE-CaPS participants (n=124) will receive US $2 per day for completing daily assessments once a day over 15 weeks (up to US $210) and US $20 per completed weekly assessment (up to US $300). Thus, participants in this arm may earn up to US $685, or US $735 if they also complete the exit interview. Participants in the control arm may earn up to US $175 in total. Compensation will be provided weekly via a reloadable study credit card [74]. Participants will not be compensated for on-demand app usage or engagement with intervention components. Although the total potential payment varies by arm, the additional amounts in SAFE-CaPS accurately reflect the increased time and effort required for intensive EMA data collection. This structure was reviewed and approved by the University of Oklahoma Health Campus Institutional Review Board (IRB). To guard against bias, total compensation received will be captured and evaluated as a covariate in sensitivity analyses.

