### Strengths and Limitations

The SAFE-CaPS study has several key strengths that distinguish it as a pioneering mHealth intervention for Black survivors with CaP. First, its culturally tailored design enables the intervention content, symptom tracking, and psychosocial support features to directly address unique survivorship challenges faced by Black men, particularly considering historical health care mistrust and disparities in symptom management. Second, the app includes real-time symptom monitoring with a tiered alert system: when a participant reports a symptom that exceeds a prespecified frequency or distress threshold, an alert is routed to the research team, who will contact the participant within 24 hours and, with the participant’s permission, notify the designated health care provider for clinical follow-up. Third, the study uses a comprehensive evaluation framework that integrates quantitative assessments (FACT-P and Patient Health Questionnaire-4 scales) with qualitative data from semistructured interviews to assess the effectiveness, feasibility, engagement, and ongoing refinement of the app. Additionally, the use of validated theoretical frameworks (WCM and UTAUT) strengthens the study’s conceptual foundation, linking clinical outcomes, psychosocial factors, and technology adoption to enhance survivorship care.

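### The article contradicts itself on how long the app is available and when alert symptoms are prompted, yet describes alerts and real-time monitoring without any time limit

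*Protocol article*

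**What the plan says.** On access, the article gives two periods. Daily EMAs states: "The SAFE-CaPS group will have access to the app-based intervention for 12 weeks". Study Recruitment and Procedure says that, after entering the download code, "they will complete the baseline assessment and have access to the app for a 12-month period".

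On prompting, there are two pictures.

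- **Year-round weekly prompts.** Study Recruitment and Procedure: "Participants will complete a weekly, app-prompted EMA throughout the study". The Abstract lists pain, urinary and bowel symptoms under EMAs that are both daily and weekly. Intervention (SAFE-CaPS) says symptom burden is tracked through weekly EMAs and quarterly surveys, and that men can log and share symptoms themselves.
- **Restricted windows.** Daily EMAs places symptom questions in the first 12 weeks and then: "Participants will also complete daily EMAs for 1 week following their 6, 9, and 12-month QoL assessments". Weekly EMAs gives that instrument one content: "The Positive and Negative Affect Schedule will be used to measure affect, consisting of two 10-item scales assessing positive and negative mood", over a stated 15 weeks. Table 1 lists pain, urinary and bowel items under daily assessments and shows no follow-up tick for them. Study Compensation pays "US $2 per day for completing daily assessments once a day over 15 weeks (up to US $210") and caps weekly payments at US $300.

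On the safeguard, Strengths and Limitations describes real-time monitoring in which, once a threshold is passed, "an alert is routed to the research team, who will contact the participant within 24 hours". Ethical Considerations lists the automated alert among the participant protections. Neither section says that prompting stops at any time.

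**The concern.** The alert system is fed by what men report in the app. If symptom questions stop for months at a time, the monitoring described as a strength and a protection is active for only part of the follow-up. The Introduction presents the problems at issue as lasting: "Long-term treatment-related side effects such as sexual dysfunction, bowel and urinary incontinence, and mobility impairments can significantly diminish QoL".

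Two things depend on which schedule is real. The first is participant protection: staff and participants need to know when a reported symptom can raise an alert. The second is interpretation. The primary endpoint is FACT-P at 12 months, and symptom monitoring is a stated mechanism. A 12-week programme with three later one-week bursts is a different intervention from 12 months of access with weekly symptom prompts, and the 12-month contrast would mean something different under each.

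**Working it through.** **Inputs.** Daily EMAs: 12 weeks, then 1 week after each of months 6, 9 and 12. Study Compensation: US $2 per day over 15 weeks, cap US $210; US $20 per weekly assessment, cap US $300; arm maximum US $685 without the exit interview. Assumptions: 12 months is 365 days; months 6, 9 and 12 fall on days 183, 274 and 365; each later EMA week starts the next day. The alternative of exact 13-week quarters (days 182, 273, 364) is also shown.

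1. **Reproduce the plan's figures.** 12 + 3 = 15 weeks; 15 × 7 = 105 days; 105 × US $2 = US $210, as stated. US $300 / US $20 = 15 weekly assessments. US $100 + 75 + 210 + 300 = US $685, as stated. The payment plan therefore matches the restricted schedule exactly. A weekly EMA all year, paid at the same rate, would come to 52 × US $20 = US $1,040.
2. **Check the 15 weekly assessments.** Weekly EMAs names the first 12 weeks plus the weeks after months 3, 6, 9 and 12, which is 12 + 4 = 16 if each is counted separately. The stated 15 is obtained if the month-3 week is not counted separately (12 + 3), which fits the Table 1 footnote that starts weekly follow-up at month 6.
3. **Daily symptom days within the year.** 84 + 7 + 7 = 98; 98 / 365 = 26.8%. The third later week occupies days 366 to 372. After week 12: 14 / (365 − 84) = 14 / 281 = 5.0%.
4. **Gaps.** Days 85–183: 99 days (14.1 weeks). Days 191–274: 84 days (12.0 weeks). Days 282–365: 84 days (12.0 weeks). With 13-week quarters the gaps are 98, 84 and 84 days (14, 12 and 12 weeks), and 99 days fall inside the year (27.1%).
5. **Compare the readings.**

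| Sections taken to govern | Symptom prompts within 365 days | Longest gap after week 12 |
|---|---|---|
| Daily EMAs, Weekly EMAs, Study Compensation | 98 days (26.8%) | about 14 weeks |
| Table 1 taken literally | 84 days (84 / 365 = 23.0%) | 281 days, about 40 weeks |
| Abstract, Study Recruitment and Procedure, Intervention | at least weekly all year | about 1 week |

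6. **Check against access.** With 12 weeks of access, all three later EMA weeks fall outside it. With 12 months, the third one (days 366–372) still does. Neither stated access period contains the stated schedule.

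**The case against.** Several points on the other side stand.

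- The restricted schedule is not the only one in the article. Read together, the Abstract, Study Recruitment and Procedure and the Intervention section give a weekly symptom prompt all year. Against that, the payment caps match the restricted schedule exactly, and the Abstract's list includes mood, so it could mean symptoms daily and mood weekly. That tilts the balance without settling it.
- The published item lists are not exhaustive. Blood in urine, constipation and blood in stool are alert triggers but appear in none of the daily lists, and the assessment details are in Multimedia Appendix 3. The lists cannot prove that nothing else feeds an alert.
- Other contacts exist. FACT-P covers pain, urinary and bowel problems and is given quarterly with PHQ-4, with the month-3 assessment near the start of the first gap. Men can log symptoms, and standard care continues in this arm. The article does not say whether any of these entries raises an alert.
- Short bursts fit the stated aim of keeping burden low, and participant instructions may sit in consent or app materials that an article condenses.

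Three stronger readings are tempting but unsupported. A reader might infer that the 24-hour contact promise is broken; that period runs from an alert, so gaps in prompting do not contradict it. A reader might picture a man in month 5 holding a silent app and feeling reassured; that takes access from one section and prompting from another, and reliance on silence is an inference the article does not make. A reader might infer that the gaps defeat a test of fewer severe symptom episodes; that phrase in Results is an expectation and not a listed outcome, and controls receive no EMAs, so EMA-detected episodes could not be compared between arms under any schedule.

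**Conclusion.** The contradiction is real and should be resolved. The article gives two access periods (12 weeks and 12 months) and incompatible accounts of when alert symptoms are asked, while the alert safeguard and the real-time monitoring claim carry no time limit.

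The size depends on which text governs. Under the detailed EMA and compensation sections, prompts fall on about 98 of 365 days (27%), with gaps of about 14, 12 and 12 weeks. Table 1 taken literally leaves about 40 weeks without daily items; this rests on blank table cells, so it carries less weight than the text. The year-round weekly reading leaves about one week. The day counts assume a 365-day year and later EMA weeks that start right after each assessment; 13-week quarters change them by one day.

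The documents do not show that men are unmonitored between windows. What they show is that the detailed schedule does not support an unqualified claim of real-time monitoring over 12 months.

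**What to change.** Reconcile the Abstract, Study Recruitment and Procedure, Intervention (SAFE-CaPS), Table 1, Weekly EMAs, Daily EMAs and Study Compensation to one access period and one prompting schedule, including where the last EMA week sits relative to the end of access. In Ethical Considerations and in Strengths and Limitations, state when prompting and alerts are active and whether self-logged entries trigger alerts. Tell participants when prompts and alerts are not active; if consent or app materials already do this, a sentence saying so is enough. Limit the real-time monitoring claim to the active windows.

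How often symptoms are asked, and the alert rule itself, remain for the sponsor to decide.

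The cost is protocol wording, one participant message and a narrower stated claim. The article reports 6 of 248 men enrolled, 2 of them in the app arm, so the correction would reach nearly all participants if made now.
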